## Abstract

**Background:**

Patients with type 2 diabetes mellitus (T2DM) have an increased risk to develop severe diabetes related complications, especially cardiovascular disease (CVD). The risk to develop CVD can be estimated by means of risk formulas. However, patients have difficulties to understand the outcomes of these formulas. As a result, they may not recognize the importance of changing lifestyle and taking medication in time. Therefore, it is important to develop risk communication methods, that will improve the patients' understanding of risks associated with having diabetes, which enables them to make informed choices about their diabetes care.

The aim of this study is to investigate the effects of an intervention focussed on the communication of the absolute 10-year risk to develop CVD on risk perception, attitude and intention to change lifestyle behaviour in patients with T2DM. The conceptual framework of the intervention is based on the Theory of Planned Behaviour and the Self-regulation Theory.

**Methods:**

A randomised controlled trial will be performed in the Diabetes Care System West-Friesland (DCS), a managed care system. Newly referred T2DM patients of the DCS, younger than 75 years will be eligible for the study. The intervention group will be exposed to risk communication on CVD, on top of standard managed care of the DCS. This intervention consists of a simple explanation on the causes and consequences of CVD, and possibilities for prevention. The probabilities of CVD in 10 year will be explained in natural frequencies and visualised by a population diagram. The control group will receive standard managed care. The primary outcome is appropriateness of risk perception. Secondary outcomes are attitude and intention to change lifestyle behaviour and illness perception. Differences between baseline and follow-up (2 and 12 weeks) between groups will be analysed according to the intention-to-treat principle. The study was powered on 120 patients in each group.

**Discussion:**

This innovative risk communication method based on two behavioural theories might improve patient's appropriateness of risk perception and attitude concerning lifestyle change. With a better understanding of their CVD risk, patients will be able to make informed choices concerning diabetes care.

**Trail registration:**

The trial is registered as NTR1556 in the Dutch Trial Register.

## Background

Patients with type 2 diabetes mellitus (T2DM) have an increased risk to develop severe complications including cardiovascular disease (CVD). The risk of these complications can be reduced by an adequate treatment with medication and by adopting a healthy lifestyle [1-3]. During the last few decades, patients are encouraged to become more actively involved in diabetes care. It is now believed that they should be the primary decision-makers in the control of their diabetes as laid down in the patient empowerment approach [4,5]. According to this approach, patients should be encouraged to use their own ability to gain mastery over their diabetes.

Informing patients on the risks to develop severe diabetes related complications enables them to make informed choices. It has been shown that patients underestimate these risks, and that they do not understand the explanation of caregivers about risks [6-13]. In contrast, it was also found that some patients are unrealistically pessimistic about their risk to develop CVD, resulting in anxiety [14,15]. Both optimistic and pessimistic patients have a reluctance in self-management [12-14,16,17]. The risk of developing complications should be explained in a way that is understandably for patients, to give them opportunities to make informed choices on their diabetes care. With clear information on the risk of developing complications, patients' risk perception may improve, which may result in a change in their attitude and intention to change lifestyle behaviour [12,14,17,18]. Although some caregivers believe that patients do not desire to take responsibility for their disease and that this responsibility might harm them [19], there is evidence that patients welcome the given responsibility. It is still unclear though how this can be achieved [20].

### Risk communication

Healthcare professionals usually explain numerical risks of developing diabetes-related complications, in percentages, frequencies, relative risks, absolute risk and 'number needed to treat' [7,21]. However, patients often do not understand the meaning of these numbers [10,11].

Specific insights on how to communicate health risks to patients have become available. Firstly, it is important to provide a clear and very simple message. This message should consist of information on what causes the risk, what are the consequences of the risk, and what can be done to prevent or treat the problem [22-26]. Secondly, the message should consist the individual risk probability in formats that patients are more likely to understand such as a visual presentation of risks rather than a presentation in percentages [18,21,23,27-32]. It is not clear what timeline for the risk presentation is preferred, but most absolute risks on CVD are predicted in a 10-year time horizon. Thirdly, positive framing, which means that the benefits of behaviour change are highlighted instead of a frame that focuses on the effect of not changing in terms of loss of healthy years of one's life, seems to help to increase patients' motivation [23,28,32-34].

In this study, we will use this broad approach of risk communication; we will not only focus on the communication of the actual risk but also on the causes and consequences of the risk by using the principles of a simple but complete message, visual representation and a positive framework to investigate if patients are able to understand the meaning of risks.

### Theoretical framework

The importance of risk communication for patients with T2DM can be explained by means of a theoretical framework. The idea is that patients are not willing to change their lifestyle if they are not informed on the reason why they should change. It is believed that people have perceptions concerning their disease, either correct or incorrect. These perceptions determine how people cope with their disease and how they manage their risks to develop severe complications. The hypothesis is that by providing understandable information on the disease by means of risk communication illness perceptions will change and, in addition, the attitude of patients concerning the importance of behaviour change.

The conceptual framework for this idea is based on two theories: the Self-regulation theory of Leventhal [35-37] and the Theory of Planned Behaviour [38,39].

Leventhal's Self-regulation Theory assumes that a patient's perceptions on the impact of diabetes and its treatment determine the attitude concerning self-management. Illness perceptions include the identity, timeline, cause, consequences and controllability of the disease [35-37,40].

The attitude to change behaviour is described in the second theory, the Theory of Planned Behaviour [38,39]. According to this theory, there are three determinants of intention to change a specific behaviour: a) attitude towards the behaviour; b) subjective norm which represent perceived social pressure by significant others to perform the behaviour, and c) perceived behavioural control, which refers to the perceived ease or difficulty to perform the behaviour. For the framework of this study, it is expected that risk communication will have impact on the attitude to change behaviour.

The plausibility of our theoretical framework will be established by measuring the components of the theories by means of questionnaires.

### Objectives

The primary objective of this study is to investigate the effect of a risk communication intervention on appropriateness of risk perception in patients with T2DM. Secondary objectives are to investigate the effects on illness perceptions, attitude, and intention to change behaviour. We will also assess patients' general satisfaction with the communication and anxiety to check for adverse effects of risk communication.

## Methods

### Design of the study

The study is a randomised controlled trial. The Medical Ethical Committee of the VU University Medical Center in Amsterdam approved the study protocol.

### Setting

The trial is conducted within 'the Diabetes Care System (DCS) West-Friesland', a managed care system that was implemented in The Netherlands in 1997. The DCS was described previously [41]. Briefly, this care system provides additional care to that of the general practitioners (GPs) in the region West-Friesland of the Netherlands. GPs in the region refer all their T2DM patients to the DCS. Each patient visits the DCS annually for a physical examination, followed by a visit to a diabetes nurse and a dietician for information and advice on their diabetes treatment. The results of this annual examination are sent to the patient's GP, who is responsible for the management of the patient and delegation of tasks to their practice nurse, according to the guidelines of the Dutch College of General Practitioners [42]. These guidelines recommend every patient with diabetes to visit a GP every 3 months. The well-organised infrastructure of the DCS with experienced medical assistants, diabetes nurses, and dieticians provides a suitable setting to implement a new intervention for patients with diabetes.

### Study population

The study population consist of newly referred patients with type 2 diabetes to the DCS. Inclusion criteria are: maximum age of 75 years and capable to fill in questionnaires in the Dutch language. Patients that have experienced a cerebrovascular accident or transient ischaemic attack will be excluded from participation in the study because they might have communication problems. Patients with other CVD may participate in the study.

Patients that fulfil the inclusion criteria will be sent an information letter as well as a concept of the informed consent form of the study. Subsequently, the patient will visit the medical assistant for their annual physical examination of the DCS concerning their standard care. In this visit, the medical assistant will also explain the purpose of the study and interest to participate in the study will be asked. All participating patients must sign a written informed consent form. After that, physical measurements are performed, which include body weight, blood pressure, and drawing of blood samples (to assess fasting blood glucose, HbA1c, total cholesterol, HDL-cholesterol and triglycerides). In addition, patients are given the first self-administrated questionnaire to fill in at the DCS.

### Treatment allocation

For intervention allocation a randomization list is drawn up using a computerized randomization computer program (Random Allocation Software version 1.0.0). Patients are randomly assigned to either the intervention group, receiving the risk communication intervention in addition to the managed diabetes care or the control group, receiving managed diabetes care only. Approximately two weeks after the first visit, patients are scheduled for either the intervention or control session to the diabetes nurse and dietician. The manager of the DCS, who is not involved in the patients' care, allocates the patient to one of the two groups on the basis of the randomisation list. The flow of the patients will be registered by a medical assistant according to a flow diagram recommended by the CONSORT statement [43]. Participants may withdraw from the study at their own request and without providing reasons. Provided reasons for withdrawal will be registered. Figure 1 shows the design of the study.

**Figure 1 F1:**
[figure not shown]
**Design of the randomised controlled trial on the effects of risk communication in patients with type 2 diabetes**.

### Blinding

Patients, diabetes nurses and dieticians cannot be blinded to the intervention. The principal investigator ([name]) remains blinded during the entire intervention.

### Interventions

#### Control group

Patients allocated to the control group receive managed diabetes care provided by the DCS. Patients are invited for a physical examination at the DCS. One or two weeks later, the patient visits a diabetes nurse and dietician, for 30 minutes each, in order to receive results from the physical examination, including an explanation of high and low values of the different lab results such as HbA1c and cholesterol, and general information and education on diabetes problems, dietary intake and physical activity.

Follow-up visits to the DCS are optional if desired. In addition, the patients will visit the GP every 3 months according to the guidelines of the Dutch College of General Practitioners [42].

#### Intervention group

Patients who are assigned to the intervention group will receive a risk communication intervention in addition to the managed care of the DCS. This means that these patients will also be invited for a physical examination, followed by a visit to the diabetes nurse and dietician, also for 30 minutes each. This visit will consist of the risk communication intervention (see below) followed by standard care of DCS. The diabetes nurses and dieticians will receive training in performing the intervention. Follow-up visits to the DCS are optional for patients in the intervention group as well. The risk communication intervention will not be performed again in follow-up visits. In addition, these patients will also visit the GP every 3 months according to the guidelines of the Dutch College of General Practitioners [42].

The risk communication consists of the previously described principles: a simple message including the cause and consequences of the risk and possibilities to improve the risk, explaining the absolute 10-year risk in natural frequencies and visual representation (population diagram), and positive framing (gain versus loss).

The intervention starts at the diabetes nurse. By means of nine variables (age at diagnosis, duration of diabetes, sex, ethnicity, smoking status, systolic blood pressure, HbA1c, total cholesterol, and HDL-cholesterol) the risk to develop CVD will be estimated with the UKPDS risk engine [44]. The diabetes nurse will explain the meaning of this risk according to an intervention protocol with six steps:

##### 1) The introduction of the risk communication

This step includes a general explanation about health related risks concerned with T2DM, including the cause and consequences of the CVD risk. This step is focused on the dimension 'cause' and 'consequences' from the Self-regulation Theory [35].

##### 2) Communication of the absolute risk according to the UKPDS risk engine

In this step, the absolute risk to develop CVD in the next 10 years will be explained in the format of natural frequencies. For example, the following sentence will be used: "Your risk to develop CVD in the next 10 years is X%. This means that of the 100 men/women of your age and with the same lab results and who also smoke/do not smoke, × will develop CVD in the next 10 years".

##### 3) Visual communication by means of a risk card

In this step, the risk will be explained again with the help of a population diagram. This diagram shows 100 people and the diabetes nurse indicates which people will develop CVD in the next 10 years.

##### 4) Positive framing: explanation that lifestyle changes can help to reduce the risk

The following step is 'message framing': translate the risk estimation into a positive message. The risk has a negative character but in this step will be explained that the patient is able to change the risk. In addition, the message will include the possibilities of how to change the risk. It is estimated that the risk to develop CVD in the next 10 years can be reduced by 30% by changing lifestyle habits, such as increasing physical activity, eating a healthier diet and to quit smoking. For example, a risk of 30% can be reduced to 21%. This means that the absolute health gain is 9%. The diabetes nurses will show this on the risk card by indicating the people that will no longer be at risk to develop CVD. In this example, 9 people will be indicated. This step is based on the dimension 'controllability' of the Self-regulation Theory [35].

##### 5) Communication with the patient for a reaction

After having finished the explanation of the risk, the diabetes nurse will ask the patient to give a reaction on the information that has been given using open questions.

##### 6) Think aloud: patient has to explain the risk him/herself

The patient will be encouraged to 'think aloud' about the risk and the meaning of the risk. It is believed that active participation will enable the patient to remember the information more easily [45].

Subsequently, the patient visits the dietician, who will continue the intervention. The dietician will start with step 6 of the intervention, the 'think aloud method' to see if the patient is able to explain what he/she has learned about his/her CVD risk. Depending on the answer of the patient, the dietician will choose one of the next steps:

• If the patient explains the CVD risk and what he/she can do to change the risk accurately, the dietician will confirm this. The remaining time of the visit will then be used for general diabetes related information and education on dietary intake and physical activity.

• If the patient is not able to explain the CVD risk or the possibilities of changing the risk, the dietician will repeat the risk communication, starting at step 2. Next, the dietician will provide usual care of the DCS on dietary intake and physical activity.

All steps will carefully be registered in order to use this information in the analysis.

Training of the diabetes nurses and dieticians

The diabetes nurses and dieticians received a training consisting of the following subsequent parts:

1) Training 1: a half day training by an experienced communication coach in health care settings and the principal investigator ([name]). The training consisted of an introduction on the importance of providing information to the patients on risks and theory on risks communication, including the definition of a risk, an explanation of absolute and relative risks, methods of risk communication and the Self-regulation Theory and Theory of Planned Behaviour. In addition, the UKPDS risk engine was explained including the scientific background of its development. The last part of this day consisted of an explanation of the intervention. In order to increase treatment fidelity to the intervention, attention was also paid to the usual care for the control group, which is standardised by means of a protocol. This training day ended with practising the intervention steps by means of role plays.

2) Pilot study: a pilot study was performed to give diabetes nurses and dieticians the opportunity to learn their skills. The coach attended visits with two patients of each diabetes nurse and dietician ('coaching-on-the-job'). She checked all steps of the intervention and the general quality of the communication and provided feedback immediately after each visit.

3) Training 2: another half day by the coach and principal investigator. During this training the coach discussed the most important issues that occurred during the pilot study to the whole group.

The training was guided by a handbook developed by the researchers and the coach including the theoretical background of risks and risk communication, the protocol for the intervention and control group, the risk card, and the role plays.

### Treatment fidelity

All diabetes nurses and dieticians were trained to perform the intervention and they all have contact with patients of both the intervention and control group. Due to practical reasons, (i.e the part-time availability of the diabetes nurses and dieticians) it was not possible to divide the caregivers into two groups.

To increase treatment fidelity we will take two measures. Firstly, we developed a protocol for both the intervention and control group that is obliged to use during the whole study period by all diabetes nurses and dieticians. Secondly, 20 tape-recordings (10 intervention patients and 10 control patients) are made to assess treatment fidelity of the diabetes nurses and dieticians.

### Outcome assessment

Primary and secondary outcome measurements are assessed at baseline, and again after 2 weeks (directly after the intervention or control visit to the diabetes nurse and dietician) and 12 weeks by means of self-reported questionnaires.

#### Primary outcome measure

Appropriateness of risk perception is the primary outcome measure. Risk perception will be measured by using a question from a questionnaire previously developed for the IMPALA study [46]. This question is 'If the mean risk of developing CVD in the next 10 years for men with diabetes is 20 of 100 men and for women 15 of 100 women, how would you rate your risk of developing CVD in the next 10 years?' In addition, at 2 and 12 weeks only, a population diagram will also be shown in the questionnaire. Patients will be asked to indicate how many of 100 people will develop CVD in the next 10 years.

Appropriateness of risk perception will be assessed by a comparison of the UKPDS score [44] of the patient with the risk perception. Appropriateness is considered as a patient with a high-risk perception while indeed having a high risk, or a patient with a low-risk perception while having a low risk [46]. According to the UKPDS risk engine, a risk of > 30% is considered high risk, a risk between 15 and 30% is an intermediate risk, a risk < 15% is a low risk.

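### The primary endpoint rule has no appropriate answer for patients whose UKPDS risk is intermediate (15–30%)

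*Protocol article*

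**What the plan says.** All the elements stand in the protocol article under Primary outcome measure.

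- **Comparison:** the patient's UKPDS score is set against the patient's risk perception.
- **Rule:** "Appropriateness is considered as a patient with a high-risk perception while indeed having a high risk, or a patient with a low-risk perception". The second clause reads in full: "or a patient with a low-risk perception while having a low risk". No third clause follows.
- **Bands for actual risk:** "a risk of > 30% is considered high risk", then "a risk between 15 and 30% is an intermediate risk, a risk < 15% is a low risk".
- **Anchors in the question put to patients:** the mean 10-year risk "for men with diabetes is 20 of 100 men and for women 15 of 100 women".

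Three other sections bear on the point. Study population sets no limit by UKPDS band. Sample size gives 84 evaluable patients per group, or 120 allowing for 30% dropout, from a t-test on 0.5 SD with 90% power. Analyses calls for intention-to-treat and assigns dichotomous outcomes to multilevel logistic regression.

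**The concern.** The rule recognises two levels of actual risk and the bands define three. A patient in the middle band satisfies neither clause, whatever the answer. These patients can learn their risk perfectly and the endpoint cannot record it.

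The article's own teaching example falls in this gap. In step 4 of the intervention, a risk of 30% is brought down to 21%. Since high means above 30%, both figures are intermediate.

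Whoever scores the endpoint must therefore choose one of these:

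- count intermediate patients as not appropriate,
- leave them out,
- merge them with a neighbouring band, or
- add a matching cell.

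These choices can give different primary results. A choice made after the data are seen would be a post hoc definition of the primary endpoint.

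**Working it through.** **1. The plan's own figure.** For two means, n per group = 2(z₀.₉₇₅ + z₀.₉₀)²/d². With d = 0.5 this is 2 × (1.960 + 1.282)²/0.25 ≈ 84.1, or 85 rounded up; the exact t-test solution is 85.03. Alpha is not stated, so two-sided 0.05 is assumed, in line with the 95% intervals. With 84 per group, power is 0.90. Dropout: 84/(1 − 0.30) = 120. The stated figures reproduce, so the fault is in the endpoint definition and not in the arithmetic.

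**2. The rule set against the bands.**

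| UKPDS risk | Band | Perception that scores as appropriate |
|---|---|---|
| below 15% | low | low |
| 15–30% | intermediate | none |
| above 30% | high | high |

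For the middle row the probability of being appropriate is 0 in both arms at baseline, 2 weeks and 12 weeks. A patient at 20% who answers 20 of 100 still fails.

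**3. How large the middle row could be (assumption).** The article gives no risk distribution. Take risk as lognormal with the mean M quoted in the question and coefficient of variation CV. Then s² = ln(1 + CV²), the median is M/exp(s²/2), and the intermediate share is F(30) − F(15).

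| Mean | CV | Low | Intermediate | High |
|---|---|---|---|---|
| 20 (men) | 0.4 | 29% | 60% | 11% |
| 20 (men) | 0.6 | 40% | 44% | 16% |
| 20 (men) | 0.8 | 48% | 35% | 18% |
| 15 (women) | 0.4 | 58% | 40% | 2% |
| 15 (women) | 0.6 | 61% | 33% | 6% |
| 15 (women) | 0.8 | 64% | 27% | 9% |

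The intermediate share m therefore runs from about 27% to 60%.

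**4. Consequence if these patients count as not appropriate.** If the true proportions p₁ and p₀ are the same in every band, the observed difference is (1 − m)(p₁ − p₀). It shrinks by 27% to 60%, and no arm can exceed 1 − m, that is 73% down to 40%.

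**5. Consequence if they are left out.** Evaluable patients per arm are 84 × (1 − m): 84 × 0.73 = 61 and 84 × 0.40 = 34.

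**6. What this does to a comparison of proportions (illustration only).** The article gives no expected proportions. Assume 50% against 74% appropriate when every patient can be scored, which gives 90% power with 84 per arm (two-sided 0.05, two proportions).

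| m | Difference, scored not appropriate | Power | n per arm, left out | Power |
|---|---|---|---|---|
| 0 | 24 points | 90% | 84 | 90% |
| 0.27 | 17.5 points | 63% | 61 | 79% |
| 0.40 | 14.4 points | 49% | 50 | 71% |
| 0.60 | 9.6 points | 30% | 34 | 53% |

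**The case against.** The strongest reply is that this is condensation. The article first states a general comparison of UKPDS score with perception, takes the high/low sentence from a cited study, and lists an intermediate band straight afterwards, perhaps meaning it to be matched too. It does not show the answer options or how an answer becomes a high or low perception, and a full protocol may do so. This stands in part: the authors may well have intended a match, a merger or an exclusion. It does not remove the point, because the article states both the rule and the bands, and as stated they do not fit together.

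Several stronger readings are tempting, and the documents do not support them.

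- **That the intermediate band is the largest.** The article gives no risk distribution, and the quoted means are anchors in a question, not the mean risk of those enrolled. Even taking them as means, the low band is larger for women at every CV in the table, and for men the intermediate band leads only up to a CV of about 0.6.
- **That power falls to one definite figure.** Putting a 0.5 SD t-test with about 50 patients per arm gives roughly 70%, but that is not the power of a dichotomous endpoint, and it rests on one assumed share.
- **That intermediate patients will be dropped.** The article says so nowhere, and dropping them would sit badly with intention-to-treat.
- **That the anchors of 20 and 15 cause misclassification that depends on sex.** This depends on an answer scale that the article does not show. With numeric answers the anchors would not determine the class. Any such error would also be expected to balance across randomised arms, costing sensitivity and not biasing the comparison.

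**Conclusion.** The rule is wrong as written: three bands of actual risk, only two ways to be appropriate, and no text elsewhere that deals with the third band. That conclusion follows from the wording alone and needs no assumption.

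Its size does need assumptions. With lognormal risk around the quoted means and CV 0.4–0.8, 27–60% of patients are affected. The effect on a difference in proportions is a loss of about that share if they score as not appropriate, given a similar effect in all bands. If they are left out, 61 down to 34 patients per arm remain of the 84. The power figures rest further on assumed proportions of 50% and 74% and serve only to show the order of magnitude. Because this is the primary endpoint, it should be settled before the data are analysed.

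**What to change.** Before the data are analysed:

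1. State how the patient's answer is turned into low, intermediate or high perception, using the same 15% and 30% cut-offs as the UKPDS score.
2. Define appropriate as agreement in any of the three bands: low/low, intermediate/intermediate or high/high.

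If the intermediate cell performs like the other two, all 84 evaluable patients per arm contribute to the endpoint.

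The absolute difference between stated and UKPDS risk could be added as a supportive analysis where a numeric answer exists. It should not replace the primary outcome: that would be a redesign, and might need a numeric item at baseline and a new basis for the sample size.

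Cost: a rewording of the definition and its scoring, with no extra visits or patients. The result becomes slightly less comparable with the two-way definition in the study from which the rule was taken.

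### The primary outcome bands cardiovascular risk in three but defines appropriate perception for two bands only, so patients with an intermediate UKPDS risk (15-30%) cannot score as appropriate

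*Protocol article*

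**What the plan says.** All of this is in the Protocol article.

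- **Primary outcome measure**, the endpoint: "Appropriateness of risk perception is the primary outcome measure". Its derivation: "Appropriateness of risk perception will be assessed by a comparison of the UKPDS score [44] of the patient with the risk perception".
- Same section, the rule: "Appropriateness is considered as a patient with a high-risk perception while indeed having a high risk, or a patient with a low-risk perception". The second case is completed by a low UKPDS risk. No third case follows.
- Same section, the bands attributed to the UKPDS risk engine: above 30% is high, below 15% is low, and "a risk between 15 and 30% is an intermediate risk".
- Same section, the question put to patients gives average 10-year risks of "20 of 100 men and for women 15 of 100 women". A population diagram answered as a number out of 100 is added at 2 and 12 weeks only. The answer format of the baseline question is not given.
- **Study population**: patients are selected on new referral, age, ability to complete Dutch questionnaires and absence of previous stroke or TIA. Predicted cardiovascular risk is not a criterion.
- **Sample size**: 84 per group for a 0.5 SD difference at 90% power with a t-test, raised to 120 for 30% dropout.
- **Analyses**: intention to treat; multilevel logistic regression for dichotomous outcomes.

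**The concern.** The rule has two categories and the risk scale has three. The two sentences stand next to each other and do not fit. The middle band has no route to success: a man with a UKPDS risk of 20% who answers exactly 20 of 100 has understood his risk perfectly, yet satisfies neither case.

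The intervention tells these patients their own risk in the same way as everyone else. If they count as failures in both arms at every visit, any benefit they gain is invisible and the overall difference shrinks. If they are treated as having no score, randomised patients leave the primary analysis, although the plan says it follows intention to treat. The text does not say which applies. Choosing between these options, or merging the band up or down, would give different primary endpoints, and the choice could be made after the data are seen.

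**Working it through.** **1. Apply the rule to each band.**

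| UKPDS risk | Perception that scores appropriate |
|---|---|
| above 30% (high) | high |
| 15-30% (intermediate) | none |
| below 15% (low) | low |

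Nothing elsewhere in the article adds an intermediate/intermediate case, merges the band into another, gives a single cut-off or excludes these patients. If a share q of patients is intermediate and they count as failures, the highest attainable proportion appropriate is 1 − q, even with perfect understanding.

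**2. Will there be such patients?** Eligibility does not screen them out. The average risks in the question are 20% for men (inside the band) and 15% for women (its lower edge). That shows the band will be occupied. It does not give q.

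**3. The plan's own sample size.** Significance level assumed 0.05 two-sided, in line with the planned 95% confidence intervals.

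n = 2 × (1.960 + 1.282)² / 0.5² = 84.06 per group, against 84 stated. Then 84 / 0.70 = 120, as stated. The exact t-test power at 84 is 89.6%. The figure reproduces, and the point made here does not rest on an error in it.

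**4. Illustration of the consequence.** Assumed, not in the document: 40% (control) versus 65% (intervention) appropriate among patients whose band can score, and the same rates in the intermediate band if it could; q = 40%; 84 evaluable per group; two-sided 0.05.

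Power = Φ[(d − 1.960 × se0) / se1], with se0 = √(2 p̄(1 − p̄)/n) and se1 = √((p1(1 − p1) + p2(1 − p2))/n).

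- *All bands can score:* d = 0.25, p̄ = 0.525, n = 84; se0 = 0.0771, se1 = 0.0746; Φ(1.33) = 91%.
- *Intermediates scored as failures:* 0.40 × 0.6 = 0.24 and 0.65 × 0.6 = 0.39; d = 0.15, p̄ = 0.315, n = 84; se0 = 0.0717, se1 = 0.0707; Φ(0.13) = 55%.
- *Intermediates left out:* n = 84 × 0.6 = 50.4, d = 0.25; se0 = 0.0995, se1 = 0.0963; Φ(0.57) = 72%.

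**5. Range over the unknown share** (same assumed rates, 84 per group):

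| q | Difference if scored as failures | Power if scored as failures | Power if left out |
|---|---|---|---|
| 20% | 20 points | 75% | 83% |
| 40% | 15 points | 55% | 72% |
| 60% | 10 points | 36% | 54% |

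**The case against.** The best defence is that the general rule is a comparison of UKPDS score with perception, and that the high/high and low/low sentence only illustrates agreement. Listing an intermediate band would make little sense unless it were used. The rule is also credited to a cited earlier study that is not at hand, and an article condenses a fuller protocol.

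This does not remove the problem. The sentence is worded as a definition, it is the only one given, and the article itself prints both the rule and the bands that do not fit it. The contradiction is on the page, so this is more than a detail left for elsewhere. The authors may well have intended three-band agreement, but the text does not say so.

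Other parts of the defence stand, and they limit what can be claimed:

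- A reader might infer that a third to a half of patients are intermediate. The document gives no risk distribution. The averages sit inside a hypothetical question, and the 30%-to-21% example in the positive-framing step is only arithmetic.
- A reader might infer that power will fall to 55%. The rates and q behind that figure are assumed.
- A reader might infer that leaving these patients out must take the sample below 84 per group. That depends on dropout and on q. With no dropout and q = 27%, 120 × 0.73 ≈ 88 per group remain. With no dropout and q = 40%, 120 × 0.6 = 72 remain, with about 85% power for 0.5 SD on the plan's t-test basis.

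**Conclusion.** The point holds as a defect in the stated definition of the primary outcome. As written, patients with a UKPDS risk of 15-30% meet neither qualifying case, whatever they answer, and are either scored not appropriate or left without a score. This follows from the text alone and needs no assumption.

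The size cannot be fixed from the document, because the share of intermediate patients is not given. The direction is clear: scoring them as failures dilutes the group difference, while leaving them out departs from intention to treat and costs evaluable patients. The fall from about 91% to about 55% or 72% illustrates how much could be at stake under 40% versus 65% appropriate, 84 per group and q = 40%. It is not an estimate for this trial. Because the defect lies in the primary outcome, it should be corrected before the outcome is scored.

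**What to change.** In Primary outcome measure, replace the two-case sentence with: risk perception is appropriate if the patient's stated risk falls in the same band (below 15%, 15-30%, above 30%) as his or her UKPDS risk. Apply the same cut-offs to both quantities at baseline, 2 and 12 weeks.

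Add one line on the baseline question. If it is answered as a number out of 100, the bands apply directly. If it is answered in categories, state in advance how they map to the three bands.

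The cost is a sentence or two in the outcome definition. At 2 and 12 weeks the population diagram already yields a number out of 100. At baseline the article does not show whether a numeric answer is collected, so the mapping may have to be written there.
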